# A protocol for a randomized clinical trial assessing the efficacy of hypertonic dextrose injection (prolotherapy) in chronic ankle instability

**DOI:** 10.1186/s13063-022-07037-7

**Published:** 2022-12-29

**Keywords:** Hypertonic dextrose injection, Prolotherapy, Chronic ankle instability

## Abstract

**Background:**

Lateral ankle sprain (LAS) is a common injury. Conservative care is not uniformly effective. Chronic ankle instability (CAI) results in up to 70% of patients with LAS in the physically active population. LAS, together with subsequent osteochondral lesions and pain in many patients, leads to the development of post-traumatic osteoarthritis, resulting in a substantial direct and indirect personal and societal health burden. Dextrose prolotherapy (DPT) is an injection-based therapy for many chronic musculoskeletal conditions but has not been tested for CAI. This protocol describes a randomized controlled trial to test the efficacy of DPT versus normal saline (NS) injections for chronic ankle instability (CAI).

**Methods and analysis:**

A single-center, parallel-group, randomized controlled trial will be conducted at a university-based primary care clinic in Hong Kong. A total of 114 patients with CAI will be randomly allocated (1:1) to DPT and NS groups. The primary outcome will be the Cumberland Ankle Instability Tool scores at 1 year. The secondary outcomes will be the number of re-sprains in 1 year, the Star Excursion Balance Test, the 5-level of EuroQol 5-dimension questionnaire, and the Foot and Ankle Ability Measure. All outcomes will be evaluated at baseline and at 16, 26, and 52 weeks using a linear mixed model.

**Discussion:**

We hypothesized the DPT is a safe, easily accessible, and effective treatment for patients with CAI. This RCT study will inform whether DPT could be a primary non-surgical treatment for CAI.

**Trial registration:**

Chinese Clinical Trial Registry ChiCTR2000040213. Registered on 25 November 2020.

## Introduction

Chronic ankle instability (CAI) is a common condition and it often results from lateral ankle sprain (LAS), especially in the physically active population [1]. Up to 70% of individuals have some type of residual symptoms, such as recurrent ankle sprains and perceived instability [2, 3]. A recent large longitudinal prospective study examined the onset of sensorimotor deficits after LAS which reported that CAI often begins shortly after the acute sprain injury, with a prevalence of 40% in 1 year after a first-time LAS, and is associated with long-term postural control deficits and multiple aberrant movement patterns [4]. Chronic joint instability together with subsequent osteochondral lesions eventually leads to the development of post-traumatic osteoarthritis [5], along with reduced physical activity levels and health-related quality of life [6, 7]. While the direct costs for treatment of isolated LAS are relatively low, compounding these are indirect costs from follow-up care, loss of productivity and leisure time, and care of long-term consequences of CAI [8, 9].

The lateral ligament complex of the ankle is composed of 3 ligaments: anterior talofibular ligament (ATFL), posterior talofibular ligament, and calcaneofibular ligament. The ATFL originates from the anterior aspect of the distal fibula, approximately 1 cm from the tip of the lateral malleolus, and it inserts on the talar body just anterior to the articular surface. The ATFL is the weakest ligament affected in most LAS injuries, and its residual laxity is the major underlying pathology of CAI [10]. Initial treatment of CAI is always conservative, which includes the use of an ankle brace or ankle tape but has no effect on proprioceptive acuity [11]. Exercise-based rehabilitation improves ankle stability in CAI, yet no consensus has been reached on the optimal exercise content and training volume [12]. Surgical interventions are often reserved for complete rupture of the lateral ligament complex or CAI which failed conservative treatment, but have associated surgical risks and high cost [13]. Therefore, the search for other minimally invasive therapies for CAI is necessary, among which injection therapy may be an option.

Dextrose prolotherapy (DPT) is an injection used to treat chronic painful musculoskeletal conditions through stimulation of tissue proliferations [14–17]. It consists of injections of hypertonic dextrose with a concentration between 10 and 25% to ligament-bone or tendon-bone system or in the intra-articular space, which is performed repeatedly at the established interval. Pre-clinical studies have suggested its mechanism of actions through initiation of a temporary inflammatory reaction with cytokine-induced tissue repair, granulation, soft tissue proliferation, and extracellular matrix remodeling [18–20]. The exposure of human tenocytes to DPT had been shown to induce an inflammatory response through the up-regulation of pro-inflammatory mediators [21]. In mouse models, DPT was found to stimulate fibroblast proliferation through activation of the Erk Pathway [22]. Soft tissues such as ligaments and collagen bundles also demonstrate a larger cross-sectional area and a better tensile strength after DPT [23–25].

Clinically, DPT has been used to treat conditions with specific soft tissue-mediated joint instability. Its strengthening effect on anterior cruciate ligament laxity had been proposed in a small clinical trial with patients having knee osteoarthritis [26, 27]. In a prospective single-arm study, patients with sacroiliac joint instability receiving DPT injections to the dorsal interosseous ligament have shown functional improvement for up to 24 months [28]. DPT provided significant relief of pain in patients with sacroiliac joint instability, and with longer effect than steroid injections [29]. Overall, rigorous evidence supporting DPT for ligament injuries is lacking; trials are limited in number, often of short duration, and lack methodological rigor.

This study aims to assess the clinical efficacy of DPT compared to normal saline injections among individuals with CAI in a randomized controlled trial (RCT). Our hypotheses are that DPT, compared with blinded saline injection, will result in improved self-reported ankle instability, function, and quality of life; reduced total number of re-sprains; and improved objectively assessed function over 1 year.

## Methods and analysis

The study is a 52-week, two-arm, parallel, superiority, RCT. The study flow has been summarized in Fig. 1. The Standard Protocol Items: Recommendations for Interventional Trials (SPIRIT) schedule of enrolment, interventions, and assessments is illustrated in Fig. 2. We follow the International Ankle Consortium Position Statement regarding the eligibility criteria for CAI and ultrasound evidence of ATFL laxity [30]. The inclusion criteria include age ≥ 18 years old; a diagnosis of CAI, defined as having at least 1 significant ankle sprain at least 12 months prior to study enrolment, defined as sprain associated with inflammatory symptoms (pain, swelling, etc.) and created at least 1 interrupted day of desired physical activity; at least 2 episodes of “giving way” in the 6 months prior to study enrollment; and a Cumberland Ankle Instability Tool (CAIT) score ≤ 24. Eligibility will be further clinically determined by the principal investigator (PI). Eligible participants will have a positive anterior drawer test (anterior talofibular ligament involvement) [31] and a length change of the ATFL under stress (maximum anterior draw position) and at rest of >20% [32]. Ultrasound has a high sensitivity of 97.7% and a high specificity of 92.3% for the detection of chronic ATFL injury [33] and is a recommended imaging modality for CAI.

**Fig. 1 Fig1:**
[figure not shown]
Flow chart of the study

**Fig. 2 Fig2:**
[figure not shown]
SPIRIT figure: schedule of enrollment, intervention, and assessment

The exclusion criteria include acute ankle sprain ≤ 6 months; complete tear of ATFL confirmed by ultrasound or magnetic resonance imaging (MRI); a history of previous surgeries to musculoskeletal structures (i.e., bones, joint structures, nerves) in either lower extremity; acute injury to musculoskeletal structures of other joints of the lower extremity in the previous 3 months that impacted joint integrity and function (i.e., sprains, fractures), resulting in at least 1 interrupted day of desired physical activity; a history of a fracture in either lower extremity requiring realignment [30]; high ankle sprain, generalized ligament laxity [34]; pregnancy; anticoagulant therapy; prior ATFL or ankle injections within 3 months; inflammatory or post-infectious ankle arthritis, such as clinically diagnosed rheumatoid arthritis, gouty arthritis, psoriatic arthritis, and septic arthritis; history of corn allergy [35, 36]; and co-morbidity or lifestyle preventing participation in the study protocol.

### Recruitment and consent

Participants will be recruited through social media and at primary care clinics in the New Territories East Region of Hong Kong. The study site is a university primary care clinic. After confirming the eligibility of the participants, the principal investigator will take approximately 15 min to describe the study goals, procedures, activities, and possible alternatives and answer all questions. Following this, interested candidates will be given 7 days to consider enrolment. The research assistant will then call the candidates for a second visit when written informed consent will be signed. After enrolment, participants will receive a study identification number and undergo baseline data collection.

### Randomization and allocation concealment

Randomization will be done in a 1:1 ratio using the Random Allocation Software [37]. The allocation sequence will be concealed from the researcher enrolling and assessing participants through the use of sequentially numbered, opaque, sealed envelopes [38]. The treatment allocation process starts when the investigator calls the personnel keeping the envelopes. The computer database is designed in such a way that treatment allocation cannot be changed after randomization. Each participant will receive the envelope and they will be asked to sign it. These envelopes will be kept by a person not involved in the care or evaluation of patients, or in the data collection or analysis. The envelopes will only be opened at 52 weeks after study completion.

### Blinding of participants and personnel

Two registered nurses not involved in participants’ care will prepare the syringes with dextrose or NS identified only by study identification numbers. The syringes will be wrapped in aluminum foil to mask the solutions. The principal investigator and the study coordinator will therefore be blinded to the group status of all subjects. The physician who conducts the injections will be blinded to the allocation group; he is also prohibited from communicating with participants. Dextrose and saline solutions are odorless and identical in color and viscosity. Participants will be blinded to their group status, knowing only their randomization group number.

### Blinding in outcome assessment and data analysis process

All data collection will be performed by trained research assistants blinded to the allocation status of the patients via face-to-face interviews. They will receive rigorous training in standardized data collection procedures. Data entry personnel external to the research team will be employed to perform data entry such that the statistician can analyze data without the need to refer to allocation information.

### Intervention descriptions

The injection procedures will be conducted under an aseptic technique by trained physicians. Following sterile preparation and injection of 1 ml 2% xylocaine as local anesthetic blebs, participants will be injected under ultrasound guidance with 25-gauge 1.5-inch needle directed to the ATFL attachment on the talus and fibula using a linear probe with an in-plane approach and peppering technique (Fig. 3a, b). We will follow the conventional prolotherapy technique prolotherapy adapted from standard prolotherapy texts to inject the ATFL at weeks 0, 4, 8, and 16 [39].

**Fig. 3 Fig3:**
[figure not shown]
**a** Injection of anterior talofibular ligament, in-plane approach under ultrasound guidance (talus end). **b** Injection of anterior talofibular ligament, in-plane approach under ultrasound guidance (fibula end)

In the intervention group, syringes will be loaded with 5 ml of 15% dextrose (D15), prepared by mixing 1.5ml 50% dextrose and 3.5 ml sterile water. In the control group, syringes will be loaded with 5 ml normal saline. In case of pain flares after injection, the subsequent injection will be commenced after the flare is subsided, or at 1 month. If participants display allergic symptoms to the injected solution, therapy will be terminated but participants will continue to be followed in their allocated group until the end of the study.

Participants will be observed for 10 min after each injection. They will be advised to take acetaminophen (500 to 1000 mg every 4 to 6 h as needed) and avoid non-steroidal anti-inflammatory drugs in the first week after injection, which may interfere with the DPT mechanism of action. Participants will be instructed on post-injection care and slow ramp-up of activity.

Participants in both groups will receive an online video (https://youtu.be/99VxZoUtEVQ) which demonstrates proprioceptive training of the foot and ankle. The video includes the practice of 6 land-based exercises (i.e., one-legged knee flexion, toe stand, one-legged stance, runner pose, cross-leg sway, and toe walk). The exercise frequency is 3 times per week, consistent throughout the study period [40, 41].

Co-interventions will be discouraged but allowed in both groups, such as conventional medication, physical therapy, acupuncture, herbal medicine, over-the-counter drugs, and other active treatments. The use of co-interventions will be tracked during the study period and assessed as co-variates.

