### Baseline and outcome measurement at 0, 16, 26, and 52 weeks

Primary outcome:The primary outcome will be Cumberland Ankle Instability Tool (CAIT) assessed at 52 weeks. The CAIT is a 9-item 30-point scale, with a lower score indicating more functional ankle instability [42]. CAIT is a widely recommended discriminative instrument for the identification of CAI with good responsiveness [43]. A validated Chinese version will be used in this study [44].

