
Sociodemographic data such as age, sex, occupation, and imaging confirmed osteochondral lesions or post-traumatic osteoarthritis will be collected and controlled as con-founders.

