### Sample size calculation

Since no previous studies have evaluated the role of DPT in CAI, we estimated our sample size based on the paper by Weight et al. which calculated the minimal clinical important difference (MCID) of CAIT in a group of athletes with CAI. In this paper, the mean change of CAIT after focused ankle rehabilitation interventions, i.e., wobble board balance training and resistance tubing strengthen training, was 4.4 (SD 5.1) whereas the control group without any intervention was −1.4 (SD 3.4), yielding Cohen *D* of 1.34 [52]. Since the sample size of Weight’s et al. was small (*n*=50), the assessment period was short (only 4 weeks), and their participants were very young (mean age 21.5), we assumed a more conservative effect size for DPT of 0.60. With alpha 0.5 and power 85%, the calculated sample size will be 102. With the dropout rate of 10%, the total sample size will be 114, with 57 at each arm.

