### Statistical analysis

We will conduct an analysis of covariance (ANCOVA) to compare the CAIT score at 52 weeks between the intervention groups with adjustment of the baseline CAIT score. For the secondary analysis, we will use ANCOVA for other secondary continuous outcome measures and logistic regression for the binary outcome. To study the trend, we will conduct generalized estimating equations models (GEE) for both primary and secondary outcomes following the intention to treat principle, i.e., all available data will be analyzed according to the group they are randomly assigned. The use of GEE also provides the means to include subjects with incomplete and use all available data to assess the treatment effect over time. Given the longitudinal nature of the clinical trial data, we assume the autoregressive covariance structure will be the best fit for the data, but the statistical fitness by using other covariance structures will also be evaluated [53].

With a clearly defined target population, efficacy and safety outcomes, and convenient data collection procedures, our trial should realize the goal of maximizing the number of participants who are maintained on the protocol-specified intervention until the outcome data are collected. We will use multivariate imputation using chained equations (MICE) to incorporate auxiliary information about the missing data. The imputation model will include prerequisite variables in the data analysis. About 10 iterations will be conducted in each imputation process with more iterations to be considered until the chain reaches convergence [54]. Twenty completed datasets will be imputed with the use of the chain equations. Rubin’s rule will be applied to combine the effect estimates [55]. This approach provides estimated standard errors and *P* values that incorporate missing-data uncertainty. We will use the statistical package SPSS version 24 (SPSS Inc., IL, USS). All statistical tests will be two-tailed with a significant level of 0.05.

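### The protocol plans post-randomisation co-interventions as covariates without naming the model, which does not match the baseline-only ANCOVA and could bias the DPT-versus-saline estimate if applied

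*Protocol article*

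**What the plan says.** Under Intervention descriptions, the protocol permits a wide range of additional care during follow-up: "Co-interventions will be discouraged but allowed in both groups, such as conventional medication, physical therapy, acupuncture, herbal medicine, over-the-counter drugs, and other active treatments". The next sentence says what will be done with that information: "The use of co-interventions will be tracked during the study period and assessed as co-variates". It names no outcome, model, time window or coding, and does not call the analysis exploratory, sensitivity or supplementary.

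The Statistical analysis section defines the primary analysis as an ANCOVA to "compare the CAIT score at 52 weeks between the intervention groups with adjustment of the baseline CAIT score". No other covariate is named there for the primary model, and none for the secondary ANCOVA, logistic or GEE models. For the GEE models it invokes intention to treat, explained as "all available data will be analyzed according to the group they are randomly assigned".

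A third statement closes the outcome section: sociodemographic and imaging variables "will be collected and controlled as con-founders". The Statistical analysis section does not mention these either.

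**The concern.** Co-intervention use is recorded after allocation. A participant whose ankle stays unstable has more reason to seek physical therapy or medication, and CAIT at 52 weeks measures that same instability. If DPT changes how the ankle does, it can also change who seeks extra care. Use is then a possible consequence of treatment and shares causes with the outcome. Blinding does not prevent this, because use can follow symptoms without any knowledge of the arm.

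A treatment coefficient conditional on such a variable is not, in general, the randomised DPT-versus-saline difference. Part of the effect may be removed or added, and the comparison within users and within non-users is no longer protected by randomisation. The protocol also leaves room for a choice on the primary endpoint: an analyst could cite one section for including co-interventions and another for leaving them out.

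**Working it through.** **1. The two statements side by side.**

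| | Intervention descriptions | Statistical analysis |
|---|---|---|
| Covariates | co-interventions recorded over follow-up | baseline CAIT only (primary ANCOVA) |
| Model | not stated | ANCOVA on CAIT at 52 weeks |
| Status | not stated | primary |

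Neither section refers to the other, so the mismatch can be read directly from the text.

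**2. The plan's own figure.** The planning assumption is "we assumed a more conservative effect size for DPT of 0.60". A two-sample t-test at two-sided 0.05 (the level given under Statistical analysis) with 85% power needs 50.86, so 51 per arm, or 102 in total. Then 102 / (1 − 0.10) = 113.3, so 114. Both stated figures reproduce. Co-interventions play no part in this calculation.

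**3. When a shift arises.** The protocol gives no co-intervention rates, so every input below except 0.60 is assumed. Results are in SD units from large simulated samples. Three cases:

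- *Treatment does not change use.* With about 40% use in both arms, the estimate is 0.60 with and without the covariate. There is no shift.
- *Treatment lowers use, and use improves the outcome, with no shared cause.* The adjusted coefficient is total effect − b × (difference in use). With b = 0.3 and use of 12.9% on DPT versus 40.0% on saline: 0.60 − 0.3 × (0.129 − 0.400) = 0.60 + 0.081 = 0.68. The shift is upward.
- *Treatment lowers use, and use shares an unmeasured cause with the outcome but has no effect itself.* With use of 16.7% versus 41.8%, the estimate falls from 0.60 to 0.49. The shift is downward.

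With a true effect of 0, the same set of scenarios gives adjusted estimates from −0.10 to +0.08 when treatment affects use. The baseline-only ANCOVA stays at about the true value throughout.

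**4. Use driven by mid-trial symptoms.** Assumptions: mid-trial and 52-week CAIT correlate at 0.7, DPT shifts both by 0.60, the log-odds of use fall by 1.0 or 1.5 per SD of mid-trial CAIT, and the co-intervention has no effect of its own.

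| Slope | Use, saline vs DPT | Unadjusted effect | With co-intervention, no baseline term | With co-intervention and baseline CAIT (assumed r = 0.5) |
|---|---|---|---|---|
| 1.0 | 56% vs 44% | 0.60 | 0.53 | 0.55 |
| 1.5 | 58% vs 42% | 0.60 | 0.48 | 0.52 |

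The last column is closest to the planned ANCOVA. Attenuation there is (0.60 − 0.55) / 0.60 = 8% and (0.60 − 0.52) / 0.60 = 13%. Without the baseline term it is 12% and 20%.

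**The case against.** The best defence is that the Statistical analysis section governs, and it already states a sound primary model. On that reading the sentence under Intervention descriptions may describe only an exploratory look, and a separate analysis plan may say so. This stands in part: a reader might infer that the primary comparison will be adjusted for co-interventions, and the documents do not establish that. But the protocol makes an affirmative statement about analysis without limiting it, so it is open to the other reading too.

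Three further inferences go too far.

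- *That the plan breaks its own intention-to-treat rule.* The rule is worded as analysis by randomised group and is attached to the GEE models. A covariate neither removes nor reassigns anyone. It changes the quantity estimated, which is a different criticism.
- *That the estimate will be biased, and towards zero.* A shift needs treatment to affect use, and use to affect CAIT or share causes with it. Co-interventions are discouraged and participants are blinded, which may keep any difference small. The direction is not fixed.
- *That power drops from 85% to about 71%.* That figure comes from putting an effect of 0.50 into a t-test with an unchanged SD. It ignores the smaller residual variance once a covariate is added, and it omits the planned baseline term. Under the assumptions of step 4, power at 51 per arm is about 72–78% without baseline CAIT and 87–90% with it. No loss of power against the planned 85% should be claimed.

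**Conclusion.** The point holds as an unreconciled statement about covariates that carries a conditional risk of bias. The protocol plans post-randomisation covariates, does not say where they enter, does not confine them to a supplementary analysis, and so does not match the baseline-only ANCOVA. If they were used in the efficacy models, the DPT-versus-saline estimate could be biased in either direction. The size for this trial cannot be computed. The illustrations (0.60 falling to roughly 0.48–0.55 under symptom-driven use of about 56–58% versus 42–44%, or rising to 0.68 under other assumptions) rest on assumed rates, correlations and effects of co-intervention. They show that the shift need not be trivial, not that it will occur.

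The sociodemographic and imaging variables are a lesser matter. Adjusting for characteristics fixed before randomisation does not carry this risk, though the covariate list should be the same wherever it appears.

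**What to change.** Under Intervention descriptions, replace the clause that makes co-interventions covariates, and carry the same text into Statistical analysis:

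- Co-intervention use will be reported descriptively by arm.
- The primary and secondary efficacy models adjust for baseline variables only, listed by name, and outcomes are analysed as observed whatever co-interventions were used.
- Any analysis that accounts for co-interventions is labelled supplementary, states the question it answers, and uses a method suited to post-randomisation events.

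The cost is two or three sentences. No new data are needed, and 102 evaluable and 114 randomised stay as they are. The Trial status section expects the last visit on 5 March 2023, after the article's publication on 29 December 2022, so the wording could be settled before the final analysis. It should be fixed before allocation is revealed.
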